### Primary outcome measures

The primary endpoint of this study is a successful healing of the syndesmosis 6 months after surgery by evaluation of MRIs of the ankle [26]. MRI scanning in the plane of the syndesmotic ligaments is the investigation of choice to evaluate syndesmosis healing. MRI images will be evaluated for degenerative changes of the cartilage of the ankle, appearance (unaffected, hyperintense signal alteration on T2, partial/complete tear), widening, and calcification of the syndesmosis. If these evaluations are ordinary, successful healing can be assumed and will be classified as healed by a senior radiologist.

Another primary outcome measurement of this study is the gait analysis 6 months postoperatively to detect biomechanical differences between both treatment groups.

Due to the pilot study character, it remains to be clarified which are the most suitable parameters to depict potential effects and differences.

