The most popular treatment option of the unstable distal tibiofibular joint is a static 3.5-mm screw fixation (FA DePuy Synthes, USA) with one or multiple screws through three or four cortices. Disadvantages of the syndesmosis screws are partial weight-bearing for at least 6 weeks, neglect of the dynamic property of the syndesmosis, and an increased risk of chronic instability as well as the potential of late diastasis due to loosening, screw breakage, or screw removal. Furthermore, syndesmosis malreduction is reported to occur in up to 50% with syndesmotic screw fixation [8, 9]. Six to 8 weeks after the initial treatment, a mandatory implant removal is required to begin weight-bearing at our trauma center. In contrast, some authors prefer to retain the syndesmotic screw in place until she breaks. Whether or not the syndesmotic screw should be removed prior to weight-bearing is still discussed [10].

In contrast to screw fixation, the flexible, dynamic TightRope® (Arthrex, Naples, FL, USA) suture button device was developed for physiological stabilization of the distal tibia and fibula. The use of this dynamic suture button device has increased rapidly over the last years. Theoretically, this suture button device allows physiological motion of the syndesmosis without need for implant removal, which may reduce the risk of recurrent syndesmotic diastasis as described after syndesmosis screw removal [11, 12].

Biomechanical investigations have demonstrated that the strength of TightRope® device is comparable to a tricortical 3.5-mm syndesmotic screw. Several recent studies assessed syndesmosis stabilization with the suture button device and comparative studies reported equivalent or better functional results in comparison to the syndesmotic screw [3, 13–16].

Instrumented gait analysis is a well-established procedure at our trauma center, which allows objective quantification of gait deviations in the context of conservative and surgical treatment in the lower extremity. For assessment, the patient is equipped with skin-based markers and asked to walk repeatedly along a 5-10-m-long walkway at self-selected speed for monitoring joint motion via optical motion tracking. Floor mounted force plates allow for determining ground reaction forces when walking across them. This so-called “standard clinical instrumented 3D gait analysis” is a modern in vivo analysis, which allows for analyzing joint motion and joint kinetics of the major lower limb joints [17, 18].

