The postoperative treatment protocol is similar in both groups. The ankle will be immobilized in a below-the-knee cast with the ankle joint at 90° for 6 weeks with partial weight-bearing. Between the 6th and 8th week, only the static syndesmosis screw will be removed in a standardized outpatient surgery. The dynamic fixation of the syndesmosis by means of TightRope® needs no removal postoperatively. Afterwards, weight-bearing can be gradually increased with approximately 20 kg per week until full weight-bearing is achieved.

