Unfortunately, a second operation for implant removal involves the risk of potential infections, increased costs for the patient, missed work days, a longer recovery time, or other complications [34]. The higher material costs of the TightRope® are largely surpassed by the reoperation costs [35].

Furthermore, other studies have demonstrated that early screw removal before syndesmosis healing increases the risk of developing a syndesmotic diastasis [36]. Schepers et al. demonstrated in their review that there was no better outcome when routinely removing syndesmotic screws [10].

The number of screws, screw size, and number of cortices are still subject to controversial discussions as well. According to the standard AO principles and depending on the injury, we use one or two 3.5-mm tricortical trans-syndesmotic screws as well as one or two TightRope® suture button devices.

Up to 30% of patients with an ankle fracture complain of residual symptoms such as pain, swelling, and movement restrictions. Clinical and radiological investigations cannot clearly identify the causes for these complaints. Additional objective information about the clinical outcome during postoperative follow-up examination are necessary and can be provided by modern investigation techniques such as gait analysis [37]. However, these modern investigation tools have not yet been used in the literature so far to compare the outcome of TightRope® and screw fixation patients.

Clinical gait analysis helps to identify the level of ground reaction forces, ankle loads, and reasons of incorrect loads or overloads. It is possible to determine parameters, like cadence (steps per minute), stride length, gait speed, or walking distance as well as parameters of the gait symmetry and the variability of the gait pattern. An incorrect marker placement on the body, the soft tissue’s variability, and other adjacent joint pathologies or deformities can lead to systematic measurement errors [38].

The primary strength of this study is its prospective randomized controlled and well-established design and follow-up examination protocol. All outcome measures and tools were validated. CT/3D scan will be performed to assess the quality of ankle reduction.

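### The widening item of the primary healed call is not comparable between arms as a measure of ligament healing, because at the 6-month MRI the TightRope is still in place and the screw is out

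*Protocol article*

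**What the plan says.** The section on primary outcomes opens by naming the endpoint and its timing: "The primary endpoint of this study is a successful healing of the syndesmosis 6 months after surgery by evaluation of MRIs of the ankle". The items are listed next: "MRI images will be evaluated for degenerative changes of the cartilage of the ankle, appearance (unaffected, hyperintense signal alteration on T2, partial/complete tear), widening", followed by calcification. They are then combined into one call, which a senior radiologist makes. The end of the list and the rule read: "widening, and calcification of the syndesmosis. If these evaluations are ordinary, successful healing can be assumed". I read this as requiring all four items to be ordinary.

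Under Surgical treatment, the implant schedule differs by arm. "Between the 6th and 8th week, only the static syndesmosis screw will be removed in a standardized outpatient surgery", whereas "The dynamic fixation of the syndesmosis by means of TightRope® needs no removal postoperatively".

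Two statements connect that difference to joint width. The Background describes the suture button as needing no removal, "which may reduce the risk of recurrent syndesmotic diastasis as described after syndesmosis screw removal"; the sentence is worded as theory. The Discussion reports from other studies that "early screw removal before syndesmosis healing increases the risk of developing a syndesmotic diastasis".

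Study setting and population gives the purpose of the 6-month MRI as judging how far the syndesmosis ligament has healed. The limitations in the Discussion do not mention that implant status differs between arms at that scan.

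**The concern.** The endpoint is named healing and its stated purpose concerns the ligament. One of its four conditions, absence of widening, can also depend on whether something is holding the tibia and fibula together at the scan. By plan that differs between arms for every patient treated as allocated.

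Take two patients with ordinary cartilage, ordinary ligament appearance and no calcification, and the same residual laxity. The one with the device in place may show normal width and be called healed. The one whose screw was removed may show widening and not be called healed. If enough patients are like this, a higher healed rate with TightRope could be reported as better ligament healing when it partly shows that the implant is still there. Masking the radiologist would not remove this, because the difference is in the joint and not in the reading.

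**Working it through.** **1. Implant status at the scan.** The MRI is at 6 months: week 26 in Study setting and population, week 25 in one sentence under Follow-up. The screw is out by weeks 6 to 8. The interval without a screw is 26 − 8 = 18 to 26 − 6 = 20 weeks (17 to 19 if week 25 is used). On either timing the screw arm is scanned without its implant and the TightRope arm with it.

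**2. Who can be affected.** All four items must be ordinary. An ankle with a visible partial or complete tear fails on appearance in either arm, however well the joint is held. Widening can change the call only where cartilage, appearance and calcification are all ordinary.

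**3. Size.** The article plans 25 patients per arm and states no healing rate, widening rate, effect size or power, so there is no figure of its own to reproduce. One patient is 1/25 = 4 percentage points of an arm. For illustration, define three quantities, all assumed:

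- q: probability that the other three items are ordinary, set equal in both arms (no true difference in ligament status)
- w: probability of widening among those patients with no device in place
- m: share of that widening that the retained device prevents from showing

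Then P(healed, screw) = q(1 − w), P(healed, TightRope) = q(1 − w(1 − m)), and the gap is q × w × m.

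Example with q = 0.8, w = 0.2, m = 1: screw 0.8 × 0.8 = 0.64; TightRope 0.8 × 1 = 0.80; gap 0.8 × 0.2 × 1 = 0.16.

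| q | w | m | Screw healed | TightRope healed | Gap (points) | Patients in 25 | Chance of p ≤ 0.05 |
|---|---|---|---|---|---|---|---|
| 0.6 | 0.05 | 0.5 | 57% | 58.5% | 1.5 | 0.4 | 3.2% |
| 0.8 | 0.10 | 1 | 72% | 80% | 8 | 2 | 5.2% |
| 0.8 | 0.20 | 1 | 64% | 80% | 16 | 4 | 15% |
| 0.9 | 0.30 | 1 | 63% | 90% | 27 | 6.75 | 50% |

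The last column is an exact enumeration of a two-sided Fisher test at 25 per arm. The test and its sidedness are my assumptions; the article gives only the 0.05 threshold.

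Over q from 0.6 to 0.9, w from 0.05 to 0.30 and m from 0.5 to 1, the gap runs from 0.6 × 0.05 × 0.5 = 1.5 points to 0.9 × 0.30 × 1 = 27 points. Among otherwise ordinary MRIs alone it is w × m, from 2.5 to 30 points; that figure must be multiplied by q before it describes an arm. If w or m is near zero, so is the gap.

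**4. With widening left out.** Both probabilities become q, and the gap from this mechanism is zero.

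**The case against.** The strongest reply is that widening belongs in the endpoint. Planned removal is part of the screw strategy, the stated objective is outcome after stabilisation with either implant, and the Background treats maintained reduction as essential. Diastasis after planned removal is then a real result of that strategy. Joint width also depends on reduction at surgery: the Background cites malreduction in up to 50% with screws, and the Discussion reports less of it with TightRope. Widening from that source is a treatment effect, not a product of the removal schedule. All of this stands, and it is why the item should be kept. It does not make a composite difference evidence about the ligament, which is how the article words the endpoint and the purpose of the MRI.

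A reader might infer that the rule as a whole measures mechanical hold in one arm and tissue healing in the other. The article does not support that: ligament appearance is graded in both arms and a visible tear fails in both. A reader might also infer that the composite is shown to favour TightRope. It is not: the Background sentence is hedged, the Discussion sentence concerns removal before healing, neither says that a retained device hides an unhealed ligament on MRI, and no rates are given.

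Finally, component-level reporting is often left to the analysis plan, and the article defers final details to one that is not shown. The point here does not rest on a missing detail; it rests on the composition of the primary rule as stated.

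**Conclusion.** The point holds for the widening item, not for the rule as a whole. As a measure of ligament healing at 6 months that item is not comparable between arms, because the plan leaves one implant in place and removes the other, and the article itself associates removal with diastasis. The likely direction on that item favours TightRope, which is also the direction of the study's hypothesis. A net advantage on the whole endpoint is an inference.

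The size is unknown. The range of 1.5 to 27 points rests wholly on assumed values of q, w and m and on equal ligament status in the two arms; the true figure may be negligible. What is at stake is the interpretation of the primary result, not the conduct of the trial.

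**What to change.** Keep the four-item composite as the primary healed call, and add three things before the database is closed:

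1. Report widening by arm as a separate outcome, labelled maintenance of reduction, and state for each arm whether the implant was in place at the MRI.
2. Compare the arms on healed with the widening item left out and the other three items unchanged.
3. State in advance that a difference in the composite that is driven by widening will not be interpreted as better ligament healing.

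This costs one more analysis and one or two table rows. The items come from the MRI reading already planned, so no new scan or visit is needed and the registered endpoint stays as it is. Replacing the rule by ligament appearance alone would cost more: it would also drop cartilage and calcification, and it would need a decision on which appearance grades count as healed. No view is taken here on whether or when an implant is removed.

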### Secondary outcome measures

Secondary endpoints and measurements will be recorded 6 weeks and 3, 6 and 12 months postoperatively. The measurements include different questionnaires mentioned above with subjective evaluation of the quality of life (assessed by the 12-item Short Form health survey [SF-12] questionnaire) [19] and pain (visual analog scale [VAS]). In addition, a self-designed questionnaire as well as the “Score of Olerud und Molander (OMAS)” [20] and “Foot and ankle outcome score (FAOS)” [27] will be used to evaluate the range of motion, deficits in daily life, symptoms after ankle fractures and after surgical treatment, and socioeconomic factors (period of time, returning back to work, and time of recovery).

## Discussion

The objective of this prospective randomized controlled single-center study is the comparison of the gait analysis, clinical and radiographic outcome after stabilization of an acute syndesmosis rupture with either a static implant (a 3.5-mm metallic screw through three cortices) or a dynamic device (TightRope®).

The study aims to investigate the clinical, biomechanical, and radiographic outcome of TightRope® as a dynamic stabilization device compared to the gold standard, the static screw device after acute syndesmosis ruptures of the ankle.

A lot of studies investigated the equality of both treatment options with numerous advantages of the suture button device over the screw fixation [28]. Zhang et al. described in their review that both devices had similar functional outcomes and postoperative complication rates. Furthermore, TightRope® device leads to a better range of motion and earlier return to work, compared to the screw fixation. Besides, TightRope® fixation groups had lower rates of implant removal, implant failure, and malreduction.

Actually, there is no human study with focus on objective biomechanical outcome measurements by using a gait analysis. Former biomechanical studies have demonstrated the advantages of the dynamic fixation of the syndesmosis only in animals or models [13, 29–31].

In the current study, we use the OMAS score, as it is the only validated assessment tool for ankle fractures. It detects clinical differences between treatment groups with a higher sensitivity and specificity as other scores [32].

In our study, weight-bearing is allowed after 6 weeks in both groups and only after screw removal in the intervention group, although many studies have proposed earlier weight-bearing with the dynamic fixation on the one hand [14, 33]. On the other hand, the static screw fixation prohibits early weight-bearing especially because of a high risk of screw breakage. These studies show that early weight-bearing is associated with a shorter recovery time as well as a quicker return to main activities.

Furthermore, the need and timing for postoperative routine syndesmotic screw removal are still subject to controversial discussions. In accordance with AO principles, elective routine screw removal prior to the beginning of full weight-bearing is carried out in our trauma center between the 6th and 8th week after surgery.

Unfortunately, a second operation for implant removal involves the risk of potential infections, increased costs for the patient, missed work days, a longer recovery time, or other complications [34]. The higher material costs of the TightRope® are largely surpassed by the reoperation costs [35].

Furthermore, other studies have demonstrated that early screw removal before syndesmosis healing increases the risk of developing a syndesmotic diastasis [36]. Schepers et al. demonstrated in their review that there was no better outcome when routinely removing syndesmotic screws [10].

The number of screws, screw size, and number of cortices are still subject to controversial discussions as well. According to the standard AO principles and depending on the injury, we use one or two 3.5-mm tricortical trans-syndesmotic screws as well as one or two TightRope® suture button devices.

Up to 30% of patients with an ankle fracture complain of residual symptoms such as pain, swelling, and movement restrictions. Clinical and radiological investigations cannot clearly identify the causes for these complaints. Additional objective information about the clinical outcome during postoperative follow-up examination are necessary and can be provided by modern investigation techniques such as gait analysis [37]. However, these modern investigation tools have not yet been used in the literature so far to compare the outcome of TightRope® and screw fixation patients.

Clinical gait analysis helps to identify the level of ground reaction forces, ankle loads, and reasons of incorrect loads or overloads. It is possible to determine parameters, like cadence (steps per minute), stride length, gait speed, or walking distance as well as parameters of the gait symmetry and the variability of the gait pattern. An incorrect marker placement on the body, the soft tissue’s variability, and other adjacent joint pathologies or deformities can lead to systematic measurement errors [38].

The primary strength of this study is its prospective randomized controlled and well-established design and follow-up examination protocol. All outcome measures and tools were validated. CT/3D scan will be performed to assess the quality of ankle reduction.

The large number of 50 patients is also remarkable. Moreover, only experienced orthopedic trauma surgeons will perform all surgical procedures which improve good external validity. The objective biomechanical outcome measurements with the aid of gait analysis are a unique characteristic which can show kinematics and functions of the ankle joint.

Limitations of the study include the diversity of ankle injury and fracture types that can bias the outcome. To minimize bias, all included patients will follow the same postoperative weight-bearing pattern.

We only perform CT/3D imaging on the fracture site. A bilateral CT investigation to detect possible anatomical variations will not be performed. A 1-year follow-up involves the danger of not being able to detect long-term complications as degenerative changes or osteolysis that could be a result of either a malreduced syndesmosis or an initially unreported osteochondral lesion. Therefore, a longer follow-up period would be interesting to observe such possible changes in the ankle mortise (widening, osteolysis, or osteoarthrosis).

Our hypothesis is that TightRope® will provide the same biomechanical, clinical, and radiological outcome with a similar or better postoperative function of the ankle in the gait analysis. Furthermore, we assume that the recovery time and the time required to return to work is shorter in the TightRope® cohort than in the static screw control group.

The results of the study should, in biomechanical terms, therefore help to demonstrate the comparability of different treatment methods by using the gait analysis as an objective and modern measurement method.

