### Surgical treatment

The fractures will be fixed within 8 days of the initial trauma in both groups using standard AO (Arbeitsgemeinschaft für Osteosynthesefragen) [22] principles. Antibiotic prophylaxis will be given perioperatively. Open reduction and internal fixation (ORIF) of fibula fractures will be treated either with a 1/3 tubular plate with or without lag screws or in high fibula fractures with syndesmosis fixation only. Additional fractures of medial and/or posterior malleolus will be treated according to standard principles before stabilizing the syndesmosis. The distal tibiofibular joint will be reduced without direct visualization of the syndesmosis and held at its anatomical position by a reduction clamp. The ankle joint will be positioned at an angle of 90° between the tibial shaft and the foot during syndesmosis fixation in accordance with the randomization (cortical screw or TightRope®).

For the static syndesmotic screw fixation, a 2.5-mm hole will be drilled under fluoroscopic guidance, approximately 2 cm above and parallel to the distal tibial joint line from lateral to medial. If plating of the fibular fracture is necessary, the hole will be drilled through an empty screw hole. Three cortices will be drilled through and a 3.5-mm screw will be tightened.

For the dynamic fixation of the syndesmosis by means of TightRope®, a 3.5-mm hole will be drilled under fluoroscopic guidance, approximately 2 cm above and parallel to the distal tibial joint line (through a hole of the plate if present) from lateral to medial. A guide needle will be inserted from lateral to medial through the drill hole to position the oblong button over the medial tibial cortex and confirmed by X-ray. Afterwards, the assembly will be tensioned by pulling the free ends of the FiberWire on the lateral side. These will be hand-tied with a surgical knot and the round button will be firmly applied on the lateral cortex of the fibula (or onto the plate if present). After achieving an adequate syndesmotic fixation by either technique, the reduction clamp will be removed and the stability controlled under fluoroscopy.

After syndesmosis fixation, intraoperative CT/3D imaging with ISO C 3D or CIOS Spin (Siemens Healthineers GmbH, Deutschland) will be performed to evaluate syndesmosis reduction.

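### The protocol claims one weight-bearing pattern for all patients, but its own text lets loading start 0 to 2 weeks later in the screw arm

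*Protocol article*

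**What the plan says.** The limitations paragraph of the Discussion names the diversity of injury and fracture types as a possible source of bias and then adds: "To minimize bias, all included patients will follow the same postoperative weight-bearing pattern".

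Earlier in the Discussion the rule is put differently: "weight-bearing is allowed after 6 weeks in both groups and only after screw removal in the intervention group".

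The Surgical treatment section says "The postoperative treatment protocol is similar in both groups". For the first period it states: "The ankle will be immobilized in a below-the-knee cast with the ankle joint at 90° for 6 weeks with partial weight-bearing". Then: "Between the 6th and 8th week, only the static syndesmosis screw will be removed". The TightRope stays in. The sentence that follows opens with *Afterwards* and lets the load rise by about 20 kg each week until it is full. It gives no start date by arm.

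Two further statements concern what removal must precede. The Background makes removal a precondition for starting to bear weight at this centre. A later paragraph of the Discussion places removal ahead of full weight-bearing.

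Recovery time and return to work are listed under Secondary outcome measures. The Discussion expects both to be shorter with TightRope.

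**The concern.** A schedule that is common to all patients cannot also depend on an operation that only one arm undergoes, unless the other arm is held to the same date. The document does not say that it is.

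The protocol itself supplies the link to outcome. Its Discussion reports that earlier loading goes with faster recovery and an earlier return to main activities, and that a second operation costs working days and lengthens recovery. If the arms differ in when loading starts, part of the expected TightRope advantage could come from the removal and loading schedule rather than from the type of fixation.

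Randomisation does not balance such a difference, because it is part of the assigned treatment. The comparison between arms remains valid, but it is a comparison of strategies. A reader told that loading was the same in both arms would credit the implant alone.

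**Working it through.** No sample size, power or alpha figure bears on this point. The check sets the passages side by side and adds short arithmetic.

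**Inputs**
- Earliest loading in both groups: after week 6 (Discussion). I take this to mean loading beyond the partial load already allowed in the cast.
- Extra condition in one arm: screw removal (Discussion).
- Removal window: weeks 6 to 8, screw only (Surgical treatment).
- Rate of increase: about 20 kg per week (Surgical treatment).
- Visits: 6, 12, 26 and 52 weeks (Study setting and population). The gait analysis and MRI are at 6 months, given as 25 weeks in one sentence under Follow-up.

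**Reading A: the Discussion rule taken literally**
- TightRope start: week 6. Screw start: week of removal, *r*, with 6 ≤ *r* ≤ 8.
- Lag = *r* − 6, so 6 − 6 = 0 to 8 − 6 = 2 weeks.
- Gap in permitted load = lag × 20 kg, so 0 × 20 = 0 to 2 × 20 = about 40 kg, while both arms are still below full weight-bearing.

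**Reading B: *Afterwards* gives one start for both arms**
- Lag = 0. This holds if the TightRope arm also waits until the screw arm's removal date, which the text does not state. Under reading A the lag is also 0 if every screw is removed at week 6.

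**What the largest lag means at each assessment (reading A, removal at week 8)**

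| Assessment | Weeks of increased loading, TightRope | Weeks, screw | Shortfall |
|---|---|---|---|
| 12 weeks | 12 − 6 = 6 | 12 − 8 = 4 | 2/6 = 33% |
| 25 weeks | 25 − 6 = 19 | 25 − 8 = 17 | 2/19 = 11% |
| 26 weeks | 26 − 6 = 20 | 26 − 8 = 18 | 2/20 = 10% |

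The lag takes up a third of the loading period at the 3-month visit and about a tenth of it at the primary assessments.

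**What removal precedes**
- Surgical treatment: partial weight-bearing is already under way during the first 6 weeks.
- Background: removal comes before weight-bearing begins.
- Discussion: removal comes before full weight-bearing begins.

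The Background and Surgical treatment statements conflict if partial loading counts as weight-bearing. Under the last statement, load could rise before removal and only the final stage would be delayed. No single schedule follows from the three.

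**The case against.** The strongest reply is that the Surgical treatment section, read alone, can describe one schedule for everyone: six weeks in a cast, screw removal where it applies, then the same gradual increase. Only the removal is limited to the screw arm. This stands, and the conflict therefore rests mainly on the Discussion's conditional clause. That clause is still in the text, and nothing states a common start.

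It can also be said that the common pattern is offered against differences between injury types, not between arms. That is a fair reading of its place in the paragraph. The sentence still covers all included patients without qualification. In addition, removal and its burdens are openly described, so the second operation is not hidden.

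A reader might infer more than the documents support:
- **That the primary endpoints are compromised.** They are assessed at 6 months, long after either start date.
- **A date of full weight-bearing in each arm.** Neither the initial partial load nor the full load is given, so only the lag can be derived.
- **That the number of implants differs by arm.** The Discussion says "we use one or two 3.5-mm tricortical trans-syndesmotic screws as well as one or two" suture-button devices, depending on the injury. The rule is the same in both arms, and injury type precedes treatment.
- **That the arms are confused in the analysis.** The Discussion attaches screw removal to the intervention group but elsewhere treats the screw as the standard comparator and writes of TightRope as the "cohort than in the static screw control group". This is a slip of labelling; elsewhere the arms are named by device.

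**Conclusion.** The concern holds in a limited form. The protocol claims a common weight-bearing pattern that its other passages do not secure. Under the literal reading of the Discussion, the screw arm may start loading 0 to 2 weeks later, or 0 to about 40 kg behind. Two weeks is the extreme; the lag is zero if all screws come out at week 6 or if both arms share one start.

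The consequence falls mainly on the 3-month scores, recovery time and return to work. That it is modest for the 6-month MRI and gait results is a judgement from the timing, not an estimate of effect. The arm label and the implant count are separate, minor inconsistencies and do not show that loading differs.

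**What to change.** 1. The investigators reconcile the Background, the Surgical treatment section and both Discussion statements into one weight-bearing statement: when loading may increase in each arm, and what screw removal must precede. Which rule applies is for them to decide; none is proposed here.
2. If the reconciled pattern is not the same in both arms, withdraw the claim that it is. State that recovery time and return to work compare treatment strategies: implant, removal and the loading schedule that results.
3. In that case, report by arm the dates of screw removal, of the start of increased loading and of full loading.
4. As minor corrections, make the arm label in the Discussion consistent. Also reconcile the single screw in Surgical treatment ("Three cortices will be drilled through and a 3.5-mm screw will be tightened") and the single device described there with the one or two allowed in the Discussion.

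The cost is some rewording and a few dates that the scheduled visits can supply. The downside is that conclusions on recovery and return to work would then apply to the strategies, not to the implant alone.
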